**Figure 1 FIG1:**
[figure not shown]
Study design. The arrows depict the patient flow and the schedule for follow-up visits. Patients diagnosed with triglyceridemia and coronary artery disease are assessed to confirm that their triglyceride levels are 150 mg/dL or higher. Those who meet the inclusion criteria will receive one of the study drugs within one day of randomisation (indicated by the grey arrow). Following drug administration, there is a required follow-up period lasting 12 weeks (shown with a blue arrow). After the 12-week period, patients who provide consent for continued monitoring will enter an extended follow-up phase (indicated by the dotted arrow). During this phase, any modifications to the assigned medication are prohibited. EPA: eicosapentaenoic acid; RHI: reactive hyperemia index

Assessments to be performed during the study period are presented in Table 1. At the baseline, 12 weeks, and 24 weeks, the same data will be collected, while baseline assessments will include demographic data and medication history. Endothelial function will be assessed using RH-PAT (Endo-PAT2000; Itamar Medical, Caesarea, Israel). The follow-up at four weeks will be performed at four weeks for safety monitoring. Safety assessments will include adverse event monitoring and regular laboratory tests for hepatic and renal functions. Medication adherence is monitored by verbal confirmation at the time of the visit. As the RHI is affected by exercise and medication, no major lifestyle changes are allowed during the study period, and changes in medication are prohibited.

**Table 1 TAB1:** Assessments during the study period.

Assessment	Enrollment	Study follow-up period			Discontinuation (at any time)
		4 weeks	12 weeks (±4 weeks)	24 weeks (±4 weeks)	
Medical examination	×	×	×	×	×
Written informed consent	×				×
Clinical symptom	×	×	×	×	×
Adverse events		×	×	×	×
Treatment discontinuation		×	×	×	×
Vital signs	×	×	×	×	×
Blood pressure	×	×	×	×	×
Body weight	×		×	×	×
Laboratory tests	×	×	×	×	×
Reactive hyperemia index	×		×	×	×

RH-PAT

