The safety analysis will focus primarily on the safety analysis population (SAFETY), which includes all patients who receive at least one dose of the study drug. Patients who withdraw before receiving any dose will not be included in SAFETY, while those who withdraw for other reasons will remain part of the analysis. This safety evaluation will use an as-treated methodology, analysing data based on the actual treatment received. The assessment of adverse events will be performed using logistic analysis.

Following amendments to the regulations under the Infectious Diseases Act in May 2023, medical restrictions in Japan have been relaxed. This change will be analysed through a sensitivity study to determine whether there are any differences in primary outcomes in the population before and after this amendment.

The planned comparisons are predefined and analyses are performed using a two-way approach. A P-value of less than 0.05 will be used as the criterion for statistical significance. All statistical analyses will be performed using IBM SPSS Statistics for Windows, Version 25 (Released 2017; IBM Corp., Armonk, New York, United States). The statistical analysis plan will be developed jointly by the principal investigator and a biostatistician before patient recruitment is completed and the database is closed.

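### The logistic analysis of adverse events takes no account of follow-up time, although follow-up beyond week 12 is optional; unequal continuation between arms could modestly distort the safety comparison

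*Protocol article*

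**What the plan says.** The safety paragraph of the Analysis Plan (protocol article, Statistical analysis) names one method: "The assessment of adverse events will be performed using logistic analysis". The safety population is the one "which includes all patients who receive at least one dose of the study drug". Patients who withdraw before any dose are left out, but "those who withdraw for other reasons will remain part of the analysis". Grouping is by treatment actually received.

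The Figure 1 legend sets the follow-up: "there is a required follow-up period lasting 12 weeks", and then "After the 12-week period, patients who provide consent for continued monitoring will enter an extended follow-up phase". Table 1 schedules adverse-event assessment at 4, 12 and 24 weeks and at discontinuation, with a window of 4 weeks either side of the 12- and 24-week visits. The Study design section describes the trial as open-label. The Outcomes text lists safety among the secondary aims, although Table 2 does not include it.

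Nothing in the article limits the adverse-event comparison to a common period or relates events to time observed. The 30-day rule under Study oversight and organisation concerns reporting of significant events. It runs from each patient's last dose, so it does not equalise observation time.

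**The concern.** By the article's own schedule, a patient in the safety population may be observed for less than 12 weeks (early withdrawal), about 12 weeks (8 to 16 with the visit window) or about 24 weeks (20 to 28). A logistic model of event yes/no treats these patients alike.

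That does no harm to a null comparison if the mix of observation times is the same in both arms. It need not be. Consent to the extension comes after randomisation, from patients who know which drug they take. If event-free patients in one arm continue more often, that arm has more time in which to record a first event at the same underlying risk. The between-arm odds ratio for a stated secondary aim could then show a difference that is not there, or shrink one that is.

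**Working it through.** The article gives no adverse-event rate, no expected extension uptake and no precision for the safety comparison, so there is no stated figure to reproduce. What follows is an illustration.

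**From the article:** required follow-up 12 weeks; optional extension to 24 weeks; 50 patients per arm.

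**Assumed:** 12-week event risk p between 5% and 30%; the same constant hazard in both arms through week 24, so the true ratio is 1; a fraction u entering the extension; continuation independent of earlier events; no other losses.

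**Formulae.** With a constant hazard, the 24-week risk is 1 − (1 − p)², which exceeds p by p(1 − p). The expected proportion with an event in an arm is therefore

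R = p + p(1 − p) × u,

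and the odds ratio is [R₁/(1 − R₁)] / [R₂/(1 − R₂)].

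**Uptake 80% versus 60%:**

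| p | R at u = 0.8 | R at u = 0.6 | Odds ratio |
|---|---|---|---|
| 5% | 0.05 + 0.0475 × 0.8 = 0.0880 | 0.05 + 0.0475 × 0.6 = 0.0785 | 1.13 |
| 10% | 0.10 + 0.09 × 0.8 = 0.172 | 0.10 + 0.09 × 0.6 = 0.154 | 1.14 |
| 20% | 0.20 + 0.16 × 0.8 = 0.328 | 0.20 + 0.16 × 0.6 = 0.296 | 1.16 |
| 30% | 0.30 + 0.21 × 0.8 = 0.468 | 0.30 + 0.21 × 0.6 = 0.426 | 1.19 |

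With 50 per arm, an unadjusted two-sided 5% test would reject in about 5% to 8% of trials, against about 5% with equal uptake of 70% in each arm, where the odds ratio is 1.00. A wider gap, 90% versus 50%, gives odds ratios of 1.28 to 1.41 and rejection in about 6% to 15%.

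**Masking.** Let the true hazard ratio be 1.5, with a comparator 12-week risk of 10% to 20%. Equal uptake (70% in both arms) gives odds ratios of 1.56 to 1.64. If the higher-risk arm continues at 60% and the other at 80%, these fall to 1.37 to 1.40.

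**Whose uptake matters.** The added term p(1 − p) × u concerns only patients who are event-free at week 12. Take p = 30% in both arms. In one arm 80% of all patients continue. In the other, 80% of event-free patients but only 13.3% of those with an event continue. Overall uptake in the second arm is 0.7 × 0.8 + 0.3 × 0.133 = 0.60, yet R is 0.468 in both arms and the odds ratio is 1. A gap in overall uptake is not enough; the gap must be among patients still free of the event.

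**The case against.** The strongest defence is that the article names a method and no window. Logistic analysis would serve well for a first-dose-to-week-12 comparison, and the analysis plan, which the article says is to be written before recruitment is completed and the database is closed, may set one. That is fair, and it is one reason the point is minor. It does not remove the point: the article itself pairs a method without a time term with optional follow-up, adverse-event collection to week 24 and retained early withdrawals, and as stated these do not fit together.

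A reader might also infer that the arm tolerated worse would look safer because its patients stop early. The documents do not support that. A patient who stops because of an adverse event is already a yes: Table 1 records adverse events at discontinuation, and later withdrawals stay in the safety population. Further follow-up cannot change that patient's value for that outcome.

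The remaining objections stand as limits on size. The uptake figures are assumed, and nothing in the article suggests an imbalance. If decliners are mainly patients who already had an event, or if events cluster early, the effect is smaller than illustrated. With about 50 per arm, imprecision would outweigh a distortion of this order. No safety hypothesis or power claim is made.

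**Conclusion.** The point holds in conditional form. As written, the adverse-event odds ratio could mix event risk with observation time if event-free patients continue, or are lost for other reasons, at different rates by arm. At an assumed uptake of 80% versus 60% the spurious odds ratio is 1.13 to 1.19; with equal uptake there is none. These figures rest on a constant equal hazard and on continuation independent of earlier events, neither of which the article can confirm.

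A reader might go further and conclude that the safety comparison will be biased. The documents do not show that, because they give no uptake by arm. The primary endpoint, the 12-week change in lnRHI, is untouched. Minor severity, moderate confidence.

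**What to change.** State in the analysis plan, before the database is closed, that:

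- the logistic comparison of adverse events covers a common window, first dose to week 12, counted in time since first dose because the 12-week visit itself may fall anywhere from week 8 to week 16;
- events from week 12 to week 24 are reported separately by arm, among patients who entered the extension;
- events per patient-time, or time to first event, are given by arm for the whole period, with the total time observed.

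Under equal constant hazards, the common window and the patient-time rate both return a ratio of 1 whatever the extension uptake, provided that loss of follow-up is not itself related to event risk.

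The cost is wording only. The Safety outcomes section already has the timing of each event recorded, and sample size and trial conduct do not change. The small downside is that late events move from the headline comparison to a separate table.

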Other exclusion criteria include the use of fibrates or omega-3 fatty acids within 12 weeks prior to informed consent, the use of phosphodiesterase-5 inhibitors, fasting TGs over 500 mg/dL within 12 weeks prior to informed consent, and failure to meet LDL-cholesterol management criteria (>100 mg/dL, based on Japan Atherosclerosis Society Guidelines for Prevention of Atherosclerotic Cardiovascular Diseases 2017) within 12 weeks prior to informed consent. Patients with secondary dyslipidemia, including drug-induced dyslipidemia, or primary dyslipidemia, including familial hypercholesterolemia, are also excluded. Furthermore, exclusion criteria include alcoholism, diabetes mellitus with poor control (hemoglobin A1c >9.5%) or type 1 diabetes mellitus, vasospastic angina and microvascular angina, and a life expectancy of fewer than six months.

Study procedures and randomisation

The flowchart of the study is illustrated in Figure 1. Patients fulfilling all criteria and who will provide written informed consent to participate in this study will be randomly assigned (1:1) to the pemafibrate group (0.1 mg twice daily, with dose adjustments up to 0.2 mg twice daily) or EPA group (900 mg administered two to three times daily). The aim of dose escalation is to achieve a fasting TG level of <150 mg/dL; however, this depends on the patient's response and tolerance. Randomisation will be performed using a computer-generated random sequence web response system by central randomisation. The patients will be stratified by age (<65 years, ≥65 years), sex (male, female), baseline TG levels (<250 mg/dL, ≥250 mg/dL), and baseline RHI (<1.5, ≥1.5).

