Safety will be evaluated in accordance with the Common Terminology Criteria for Adverse Events (CTCAE) version 5.0 guidelines. Any adverse events (e.g., bleeding, acute pancreatitis, severe liver dysfunction, deterioration of renal function), whether spontaneously reported by patients or identified by investigators, will be thoroughly documented. The records will include details such as the timing, clinical manifestations, management strategies, duration, resolution, and potential association with the administered medication. Causality assessment is performed by investigator judgment. For cases involving abnormal laboratory findings, patient monitoring will continue until the results normalise or are determined to be unrelated to the assigned treatment. If a participant becomes pregnant, fetal outcomes will be monitored.

Study oversight and organisation

The Steering Committee members, who were also responsible for designing the study, will supervise its implementation. Any significant adverse events occurring within 30 days following the final administration of the study drug, or beyond this period if there is a suspected link to the drug, as well as any reported pregnancies, will be promptly communicated by the investigator to both the Steering Committee and the sponsor in compliance with good clinical practice.

Discontinuation of the study for individual participants

The principal investigator or co-investigator may discontinue the study for an individual participant if they determine that it is impossible to continue the study for the participant due to any of the following reasons. The criteria for discontinuation and withdrawal are as follows: adverse events that are suspected to be caused by the study drug and that make continuation impossible (a severity of grade 4 or higher according to the CTCAE guideline), a new cardiovascular event, the participant refuses to continue or withdraws consent, and if pregnancy is confirmed.

Statistical analysis

Sample Size Calculation

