No study has investigated the changes in RHI in response to fibrates for hypertriglyceridemia treatment. However, two studies have reported a link between increased TG levels and decreased RHI, with a decrease of approximately 50 mg/dL resulting in a reduction of approximately 0.08 in lnRHI [24,25]. In addition, previous reports have examined changes in FMD, another indicator of endothelial function [15-17,19,26]. Based on these studies, a 10% reduction in TG levels has been estimated to result in a 0.4% increase in FMD. The standard deviation of FMD measurements in multicenter studies is approximately 1.3%. Assuming reductions in TG levels of 45% and 20% for the pemafibrate and EPA groups, respectively, the expected increases in FMD are 1.8% and 0.8%, with a difference of 1.0% between the two groups. When this difference was converted to a logarithmic RHI (lnRHI, as RHI follows a non-normal distribution), the difference in lnRHI between the pemafibrate and EPA groups was estimated to be 0.076, with a standard deviation of 0.11. Assuming a 25% difference in TG reduction between the EPA and the pemafibrate groups in the present study, this would equate to a 50 mg/dL reduction at a baseline of 200 mg/dL, which is in close agreement with the value predicted by the FMD and is reasonable. Using a two-sample t-test with a two-sided significance level of 5% and a statistical power of 90%, the required sample size was calculated to be 90 participants (45 in each group). Considering the possibility of dropouts during the study period, the target number of patients was set at 100 in both groups (50 in each group). Assuming a statistical power of 80%, the number of cases required would be 66, which means that even if more than 10% of cases were to be excluded, the analysis would still be possible.

Analysis Plan

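### Logistic analysis, the only method named for adverse events, can give no finite odds ratio for uncommon event types with about 50 patients per arm

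*Protocol article*

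**What the plan says.** In the protocol article, the Analysis Plan defines the safety population as the one "which includes all patients who receive at least one dose of the study drug". It adds that "This safety evaluation will use an as-treated methodology" and then gives its single statement of method: "The assessment of adverse events will be performed using logistic analysis". The general rule for testing in the same section is "A P-value of less than 0.05 will be used as the criterion for statistical significance".

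The Sample Size Calculation fixes the scale: "the target number of patients was set at 100 in both groups (50 in each group". Under Study procedures and randomisation, patients "will be randomly assigned (1:1". The Figure 1 legend says that "there is a required follow-up period lasting 12 weeks", with a further phase for patients who consent to it.

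The section on safety outcomes gives examples of what will be recorded: "Any adverse events (e.g., bleeding, acute pancreatitis, severe liver dysfunction, deterioration of renal function". The text below Table 2 counts safety among the secondary aims, although the numbered endpoints in the table do not include it.

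The article gives no expected adverse event rate. It does not say which estimator, test or covariates the logistic analysis will use, or what happens when an event type has few or no cases in an arm. A separate statistical analysis plan is mentioned but is not at hand.

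**The concern.** A logistic model suits a binary outcome that occurs reasonably often in both arms. Several of the named event types may not. Follow-up is short, and the entry criteria exclude patients with raised liver enzymes, raised creatinine, gallstones, biliary obstruction or active bleeding. With about 50 patients per arm, an arm with no cases of a given event is a realistic outcome.

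When one arm is empty and the other is not, treatment separates the data. The maximum-likelihood log odds ratio runs off to infinity, and its standard error grows faster than the estimate. Software then prints an arbitrary large odds ratio, a meaningless interval and a Wald p-value near 1. The named method therefore works worst for rare, one-sided events, where a clear summary of the difference between arms matters most.

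**Working it through.** **Inputs.** From the article: 50 patients per arm, 1:1 allocation, a safety set of all dosed patients (so close to 50 per arm), and a 0.05 criterion. Assumed, because the article gives none: true event rates p of 1%, 2%, 5% and 10%, equal in both arms.

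**The plan's own figure.** The article states no safety figure. Its sample size, the source of the 50 per arm, reproduces: 2 × (1.960 + 1.282)² × 0.11² / 0.076² = 44.02, rounded up to 45 per arm or 90 in all. Allowing for 10% dropout, 90 / 0.90 = 100. Nothing below affects that figure.

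**Step 1: how often exactly one arm is empty.** Let q = (1 − p)^50 be the chance of no events in one arm. The chance that exactly one arm is empty is 2q(1 − q). The chance that both are empty is q².

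| Rate p | q | Exactly one arm empty | Both empty | At least one empty |
|---|---|---|---|---|
| 1% | 0.605 | 0.478 | 0.366 | 0.844 |
| 2% | 0.364 | 0.463 | 0.133 | 0.596 |
| 5% | 0.077 | 0.142 | 0.006 | 0.148 |
| 10% | 0.005 | 0.010 | 0.000 | 0.010 |

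The third column is the relevant one. When both arms are empty there is nothing to compare.

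**Step 2: what the ordinary fit returns at 0/50 v 6/50.** The log odds ratio does not converge. After 19 Newton steps it is 18.2 with SE 3,448 (Wald p = 0.996). After 20 steps it is 19.2 with SE 5,684 (odds ratio about 2.2 × 10⁸, Wald p = 0.997). Further steps push p closer to 1. At 0/50 v 8/50 the Wald p after 20 steps is again 0.997.

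The order of results is perverse. For 1/50 v 8/50 the log odds ratio is ln[(8/42)/(1/49)] = 2.234 and the SE is √(1/8 + 1/42 + 1 + 1/49) = 1.081. So z = 2.07 and p = 0.039. Taking away the single event in the smaller arm makes the imbalance larger but moves the Wald p from 0.039 to about 1.

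**Step 3: other tests on the same tables.**
- Fisher, 0 v 6: 2 × C(50,6)/C(100,6) = 2 × 15,890,700/1,192,052,400 = 0.027.
- Likelihood ratio, 0 v 6: 2 × {[6 ln 0.12 + 44 ln 0.88] − [6 ln 0.06 + 94 ln 0.94]} = 2 × (−18.346 + 22.697) = 8.70, p = 0.003.
- Score, 0 v 6: z = 0.12/√(0.06 × 0.94 × 2/50) = 2.53, p = 0.012.

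| Table | Wald p (20 steps) | Likelihood-ratio p | Score p | Fisher p |
|---|---|---|---|---|
| 0 v 4 | 0.997 | 0.017 | 0.041 | 0.117 |
| 0 v 5 | 0.997 | 0.007 | 0.022 | 0.056 |
| 0 v 6 | 0.997 | 0.003 | 0.012 | 0.027 |
| 0 v 8 | 0.997 | 0.0006 | 0.003 | 0.006 |

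**Step 4: a summary that stays finite.** At 0 v 6 the risk difference is 6/50 − 0/50 = 12%. The Wilson limits are 5.6% to 23.8% for 6/50 and 0% to 7.1% for 0/50. Newcombe's method combines them. The lower limit is 0.12 − √[(0.12 − 0.056)² + 0.071²] = 2.4%, and the upper limit is 0.12 + (0.238 − 0.12) = 23.8%. If a ratio is wanted, the Firth-penalised odds ratio is finite at 14.8.

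**The case against.** A reader might infer that, under the plan as written, a one-sided cluster of adverse events would be declared non-significant and so hidden. The article does not support that.

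- **No Wald test is named.** Logistic analysis also covers likelihood-ratio, score, exact and penalised versions, and these cope with an empty arm. The choice between them is detail that an article commonly leaves to the analysis plan. This objection stands against any claim about what p-value the trial would report. It does not rescue the estimate: a valid likelihood-ratio p-value from the ordinary fit still comes with an infinite odds ratio. That p-value is also much smaller than Fisher's in these tables (0.017 v 0.117 at 0 v 4), so the choice matters.
- **Counts are not withheld.** Every adverse event is to be documented in detail, and nothing says a model result replaces the tabulation. A 6 v 0 split would be visible. This stands in full.
- **Rarity is an assumption.** The four event types are only examples, and no rates are given. For any-event comparisons, or events at 10% or more, the problem all but disappears. This also stands.
- **Size.** It is tempting to cite the 84% and 60% chances of at least one empty arm at 1% and 2%, but those include two empty arms. From 0 v 1 to 0 v 5 Fisher's test is not significant either. At an equal 2% rate, a split of 0 v 6 or more in either direction has a chance of only about 0.03%. With assumed true rates of 2% and 12%, the chance of 0 v 6 or more against the second arm is about 21%. The 0 v 6 table therefore shows the mechanism and is not an expected result.

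**Conclusion.** The point holds as a minor one about a method the article does state. For uncommon event types, the only named analysis can fail to give a finite effect estimate or usable interval. This would happen for roughly one event type in two at true rates of 1% to 2%, one in seven at 5% and one in a hundred at 10%. These figures assume equal rates, 50 patients per arm and an ordinary maximum-likelihood fit. The misleading p-value near 1 arises only if that fit is read by its Wald test, which the article neither specifies nor rules out. It does not follow that an imbalance would be concealed, or that the safety analysis fails as a whole. The primary endpoint, efficacy analyses and sample size are untouched.

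**What to change.** Replace the sentence on logistic analysis in the Analysis Plan with one along these lines: adverse events will be summarised by type as counts and percentages in each arm, with the risk difference and a score-based or exact 95% confidence interval; Fisher's exact test will be used where a p-value is wanted; logistic regression will be used only for events frequent enough in both arms to fit it. If an adjusted comparison of sparse events is needed, specify a penalised or exact logistic model, and first confirm that the stated package (SPSS version 25) supports it.

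The cost is one sentence and a little extra analysis work. Fisher's test is somewhat conservative: at 0 v 5 it gives 0.056 where the score test gives 0.022. The risk difference and its interval should therefore carry the interpretation, with the p-value secondary.
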